#### Federal and state agency administrators

Near the end of the project, we will ask state agency administrator participants to nominate administrators in other state and federal agencies with which they partner to address youth SUD services. We will invite those nominees to participate in focus groups, supplementing with our own nominations as needed to ensure broad representation of relevant agencies (e.g., SAMHSA, Centers for Medicare and Medicaid Services, Health Resources and Services Administration). Agency administrators (i.e., appointed policymakers) are the most relevant audience for discussing the implications of our findings, as they (not elected policymakers) are responsible for setting most grants administration policies.

#### Recruitment

The RAND Survey Research Group—a center specializing in quantitative and qualitative primary data collection—will be responsible for all interview and survey recruitment activities. Recruiters will contact eligible individuals using contact information from CHS, which maintains a list of SAMHSA grantees and has pre-established working relationships with the state SUD agency administrators and treatment organizations through their A-CRA training and certification activities. CHS will support all recruitment activities and help to resolve challenges that arise.

Recruiters and interviewers will use multiple methods (i.e., mail, phone, e-mail) to connect with participants and remind them about data collection opportunities and timelines, consistent with effective survey methods [64]. We will reach out to state agency administrators first, to ensure they are aware of the project and can provide input if needed, before contacting clinicians and supervisors in the same state. Interviewers will collect comprehensive contact information for follow-up. Individuals who decline participation in a given wave of data collection will still be invited in future waves, as long as they remain eligible.

In the last year of the project, the PI (first author) will provide state SUD agency administrators with information about focus groups, invite them to attend, and solicit their nominations of other (state and federal) administrators to invite. The PI will then extend email and phone invitations for the focus groups to all nominated administrators, emphasizing the relevance of the project to their agency’s mission.

For each interview, survey, and focus group, we will offer compensation of $25 per activity completed. However, we anticipate some participants will decline compensation due to organizational restrictions or viewing participation as part of their professional role.

### Data sources and collection procedures

We will collect four waves of quantitative and qualitative data from state-focused grantees, to be combined with administrative records from CHS and previously collected data from organization-focused grantees. Table 1 details the planned data collection schedule. In each wave, we will collect data (semi-structured interviews, surveys, document review) from state agency representatives and clinicians/supervisors. Treatment organizations that report no longer delivering A-CRA will complete the ongoing wave of data collection, but will only participate in subsequent waves if they begin delivering A-CRA again and thus have new information to share (we will verify at the beginning of each wave). Focus groups with state and federal agency administrators will take place in the final year and so are not included in Table 1.

**Table 1 Tab1:** Waves of planned data collection for state-focused grant cohorts

Grant cohort (years)	Target # of organizations	Expected # of respondents	Data collection waves: years since funding ended			
			Wave 1 (2021–2022)	Wave 2 (2022–2023)	Wave 3 (2023–2024)	Wave 4 (2024–2025)
(1) 2013–2017	7 states 37 organizations	7 state agency administrators 33 clinicians 47 supervisors	4 years Post-funding	^a^5 years post-funding	*NA*	*NA*
(2) 2012–2018	7 states 33 organizations	7 state agency administrators 29 clinicians 42 supervisors	3 years Post-funding	^a^4 years post-funding	^a^5 years Post-funding	*NA*
(3) 2017–2021	5 states 21 organizations	5 state agency administrators 19 clinicians 27 supervisors	0 years Post-funding	^a^1 year post-funding	^a^2 years Post-funding	^a^3 years Post-funding

In each data collection wave, we will collect semi-structured interviews from all eligible participants, web-based surveys from eligible clinicians and supervisors, and grant-related documents for review from eligible state agency administrators

*NA* not applicable (i.e., data are not collected because the data collection wave falls more than five years post-funding)

^a^ Treatment organizations that reported not sustaining the Adolescent Community Reinforcement Approach (A-CRA) in the previous wave will not be eligible unless they report having restarted A-CRA delivery since the previous wave

We will collect data via secure methods (telephone for interviews, Confirmit for surveys, Zoom for Government for focus groups). We will obtain informed consent for each activity, and all data collection will be voluntary. We will not collect personally identifiable information; we will de-identify each participant’s data and assign them a unique identification number.

Next, we describe each data collection activity, followed by the details of specific measures to be collected. In addition, Tables 2 and 3 provide summaries of the data collection activities used to evaluate penetration and sustainment outcomes, respectively.

**Table 2 Tab2:** Data collection activities for comparing A-CRA penetration outcomes between grant types

Activity	Measures	Participants	Time	Compensation	Relevant Aims^a^
Administrative data from CHS		Clinicians, supervisors^b^	n/a	n/a	
	Proportion certified				Aim 1a, 1b, 3
	Descriptive data about fidelity scores				Aims 1a, 1b
Web survey (Wave 1)			30 min	$25	Aims 1b, 3
	External support [65]	Supervisors^b^			
	Leadership support (ILS [66])	Clinicians^b^			
Semi-structured interviews (Wave 1)			45 min	$25	Aims 1a, 1b, 3
	Organization-reported barriers/ facilitators of A-CRA implementation	Clinicians, supervisors^b^			
	State agency-reported barriers/ facilitators of A-CRA implementation	State behavioral health agency administrators			
Document review	A-CRA implementation-related documents	State behavioral health agency administrators	as needed	n/a	Aims 1a, 1b, 3

*A-CRA* Adolescent Community Reinforcement Approach, *CHS* Chestnut Health Systems, *ILS* Implementation Leadership Scale

^a^See Fig. 1 for details of the project aims and how they relate to each other

^b^Data collected from organization-focused grantees in the previous project will be included in the analysis

**Table 3 Tab3:** Data collection activities for comparing A-CRA sustainment outcomes between grant types

Activity	Measures	Participants	Time	Compensation	Relevant Aims^a^
Semi-structured interviews (all waves)			45 min	$25	Aims 2a, 2b, 3
	*A-CRA supervisor knowledge	Supervisors^b^			
	*Number of certified therapists	Supervisors^b^			
	*Number of certified supervisors	Supervisors^b^			
	*A-CRA usage	Supervisors^b^			
	*A-CRA dosage	Clinicians^b^			
	*Supervision frequency	Clinicians^b^ Clinicians^b^			
	*Supervision content				
	*Use of session review	Clinicians^b^			
	*A-CRA training quality	Supervisors^b^			
	Organization-reported barriers/ facilitators of A-CRA sustainment	Clinicians, supervisors^b^			
	State agency-reported barriers/ facilitators of A-CRA sustainment	State behavioral health agency administrators			
	Impact of COVID-19 on A-CRA sustainment	Clinicians, supervisors, state behavioral health agency administrators			
Web survey (all waves)			30 min	$25	Aims 2a, 2b, 3
	*A-CRA clinician knowledge	Clinicians^b^			
	Sustainment capacities (PSAT) [67]	Clinicians, supervisors^b^			
	External support [65]	Supervisors^b^			
	Leadership support (ILS [66])	Clinicians^b^			
Document review	A-CRA sustainment-related documents	State behavioral health agency administrators	as needed	n/a	Aims 2a, 2b, 3

*A-CRA* Adolescent Community Reinforcement Approach, *ILS* Implementation Leadership Scale, *PSAT* Program Sustainability Assessment Tool

^*^An element that is used to calculate the 10-element A-CRA sustainment outcome measure [68]

^a^See Fig. 1 for details of the project aims and how they relate to each other

^b^Data collected from organization-focused grantees in the previous project will be included in the analysis

#### A-CRA certification records

In year 1, CHS will create a database of penetration outcomes for all sampled treatment organizations. The database will detail the certification levels achieved during the grant period by each clinician and supervisor. Given the link between A-CRA fidelity and clinical outcomes [14, 16, 17], CHS will include each certified individuals’ fidelity data from sessions rated by trained CHS staff.

#### Semi-structured interviews

The interview protocols will use a combination of open-ended questions and focused, standard probes [69]. Protocols will be tailored to each participants’ role, and for treatment organizations, whether the organization is still delivering A-CRA; see Additional file 2 for copies of all Wave 1 protocols. The interviews will gather information about the state- and/or organization-level approaches to disseminating A-CRA, how the implementation of A-CRA was supported during the funding period (in the first interview only), how sustainment of A-CRA has been supported or discontinued post-funding, and sustainability planning. State administrators will also be asked about the infrastructure (e.g., training, policy development) developed during their grant period and plans to sustain those activities. Clinicians and supervisors will also be asked questions from our 10-element composite measure of A-CRA sustainment [68] (specified in Table 3). For organizations that did not sustain A-CRA, some questions will be anchored to the 6-month period prior to A-CRA discontinuation to allow comparable information to be collected. Initial interviews are anticipated to take 45 min, and subsequent interviews will be shortened (focusing on changes since the last wave) to approximately 30 min. We plan to audio-record and transcribe interviews.

#### Previously collected interviews

As noted previously, we collected semi-structured interviews from 169 clinicians and supervisors at organization-focused grantee organizations [32, 34]. The interviews were collected across three waves up to 5 years post-funding. These data will be combined with interview data from state-focused grantees for the planned analyses. As much as possible, the interview protocols for the current project were adapted from those used in our prior work, to ensure comparability of findings. We also grounded the protocols in the EPIS framework, to ensure we consistently ask about multi-level influences on A-CRA outcomes while distinguishing between implementation and sustainment phases.

#### Clinician surveys

Following each interview, clinicians and supervisors will be sent a web-based survey that collects standardized measures of multi-level contextual influences on A-CRA penetration and sustainment (again grounded in EPIS), one A-CRA sustainment element (see Table 3), potential moderators and mediators (see Fig. 1), and other descriptive information. As with interviews, the survey items will be tailored to the participant’s role and A-CRA sustainment status; again, some non-sustainer questions will be anchored to 6 months prior to discontinuation. The surveys are designed to take ~30 min to complete. See Additional file 3 for all Wave 1 survey items.

#### Previously collected surveys

Again, we will combine the newly collected survey data with previously collected waves of survey data from the clinicians and supervisors in our previous project [32, 34]. The measures collected in this project will be a subset of those used in our previous surveys to ensure comparability. However, we also supplemented the survey items with a few recently published measures that capture relevant descriptive variables (e.g., financial status, self-reported sustainment).

#### Document review

We will ask state administrators to identify and share documentation of state-focused grant activities for qualitative review. This method can provide useful insights into complex systems-level processes (like A-CRA implementation and sustainment) when interpreted alongside other qualitative and quantitative data [38, 70]. We will solicit documents related to the presence of, the extent of (e.g., number/frequency), and plans to maintain various state EBP infrastructure components listed in the Requests for Proposals from SAMHSA state-focused grants. Examples include grant progress reports and related data, contracts with A-CRA treatment organizations, and strategic planning tools. In interviews, state administrators will identify documents to be shared; the PI will follow up via email or phone to establish any needed confidentiality/data sharing agreements and secure the documents.

#### Focus groups with federal and state agency administrators

For identifying policy implications (aim 3), where it is important to distinguish among experts’ differing and nuanced viewpoints, focus groups are an ideal data collection method [69]. Following the final interview wave, we will hold virtual focus groups (via video conference) with state SUD agency administrators and other (state and federal) administrators. We will arrange three state-level groups, each grouping together states that had similar experiences with A-CRA; the federal administrator group will be separate. Before each group, we will ask attendees to review a policy brief [71, 72] that we will create outlining (a) key financing issues motivating this project and (b) preliminary findings. In each 45-min group, the focus group leaders (a combination of the first three authors) will review the policy brief, then engage attendees in a discussion of implications for integrating the findings into EBP-focused federal grant policies. We will take detailed field notes plus audio-record and transcribe focus groups.

### Measures

#### Grant type

We will determine participants’ involvement in SAMHSA grants based on CHS records. We will verify that determination during the consent process and with questions at the start of each interview.

#### Outcomes

As recommended for evaluating implementation strategies [28, 73, 74], we will compare the impacts of organization-focused versus state-focused grants using key implementation outcomes [23, 24, 28] for A-CRA: penetration (aim 1) and sustainment (aim 2).

##### Penetration

We define penetration as the proportion of providers (i.e., clinicians and supervisors) in a service system that were certified in A-CRA during active implementation. We will use CHS administrative records to define and measure penetration (see Table 2). Potential providers (i.e., the denominator) will include all individuals eligible for training and/or certification activities at a treatment organization during the state-focused grant period; the grant funding period will be treated as active implementation. Certification status will be based on CHS’s standard definitions for different levels and types of A-CRA certification.

A-CRA clinician certification is based on proficient demonstration of A-CRA procedures, which are 19 clinical techniques or activities used by clinicians (e.g., functional analysis of substance use, problem-solving, communication skills); first-level certification indicates proficiency in nine basic procedures, and full certification indicates proficiency in every procedure [13]. Further certification for proficiency with transition-age youth (ages 18–25) is also available and considers two additional procedures. A-CRA supervisor certification is based on proficient demonstration of supervision-specific skills and knowledge, as well as the ability to accurately and reliably rate A-CRA sessions. We will construct several penetration variables, representing the percent of participants achieving any certification as well as first-level, full, transition-age youth, or supervisor certifications.

We will also verify that each certified individual achieved adequate A-CRA fidelity, defined as an average competence rating of ≥3 out of 5 across the relevant activities for a given A-CRA certification (i.e., procedures in session recordings, supervisors’ competence in rating sessions) following past research [14, 16, 17]. We will calculate average fidelity scores that contributed to each individual’s clinical (first-level, full, transition-age) and/or supervisor certification; the same ratings can contribute to all clinical certifications, so these cannot be calculated separately. We will also calculate descriptive measures for each certification type characterizing time to certification, number of session recordings reviewed, and procedure-specific scores.

##### Sustainment

We define A-CRA sustainment over the 5-year post-grant period using a 10-element measure developed in our previous research [68], which captures the ongoing quality of treatment delivery, staffing, and supervision (see Table 3). These elements are pragmatic [75] to collect from treatment organizations and center on program-level processes, rather than clinical outcomes, as recommended for sustainment measures [76].

The A-CRA sustainment elements are collected via interviews (5 from supervisors, 4 from clinicians) except for the A-CRA knowledge test for clinicians, which is collected through the web-based survey to match how the test is typically administered. Each element will be assessed as follows: (1) clinician knowledge via a 10-item multiple choice survey, (2) supervisor knowledge using a 15-item true/false questionnaire, presence of certified (3) clinicians(s) and (4) supervisor(s) is self-reported and verified with CHS records, (5) usage by the self-reported percent of eligible youth receiving A-CRA in the past six months, (6) dosage by clinicians’ self-report of the number of sessions delivered (12–14 prescribed), clinicians also report whether clinical supervision (7) occurs biweekly, (8) involves six key activities, and (9) includes a review of recorded sessions, and (10) quality of A-CRA training plans submitted by supervisors will be rated by CHS staff (i.e., percentage of expected training components included). A composite A-CRA sustainment score is created by normalizing each element (on a 0 to 1 scale, averaged across all ratings from the same treatment organization), then summing the normalized scores (i.e., composite scores range from 0 [no] to 10 [complete] sustainment) [68].

We will also measure clinicians’ and supervisors’ global ratings of A-CRA sustainment using the newly published, three-item Provider Report of Sustainment Scale [77]. This offers a point of comparison for our primary sustainment measure.

#### Mechanisms

We will also examine components of the mechanisms [78, 79] by which organization-focus and state-focused grants influence A-CRA implementation outcomes. This will include testing for mediation of sustainment outcomes and moderation of both penetration and sustainment outcomes. All variables will be captured through the web-based surveys.

##### Penetration

We will test two a priori moderators of A-CRA penetration outcomes: outer-context reimbursement for services (“external support”), and inner-context leadership support for implementation [49, 80, 81]. We will capture external support using a series of survey items designed for adolescent treatment providers [65] that ask supervisors to report what percentage of treatment for youth is reimbursed from various sources (e.g., Medicaid, juvenile justice contracts); we will consider both the total proportion of youth treatment receiving external support and patterns of funding as potential moderators. We will measure leadership support using the 12-item Implementation Leadership Scale [66], which measures clinician perceptions of their supervisors’ leadership qualities (proactive, knowledgeable, supportive, perseverant) toward EBPs using a five-point scale (0=“not at all,” 4=“very great extent”). We will calculate an average score across all items. Note that our previous work examined leadership support toward EBPs in general among organization-focused grantees [33]; we will collect the same measure again for comparability, but because we did not previously find leadership support predicted sustainment outcomes, we will administer a second version of the Implementation Leadership Scale to explore the role of A-CRA-specific support in our sample.

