##### Sustainment

We expect that the moderating effect of leadership [66] will hold true for A-CRA sustainment. We also expect changes in external support [65] during the sustainment period to function as a mediator variable, because state-focused grants might influence the availability of funding. Furthermore, we anticipate additional moderators and mediators based on the eight domains of EBP sustainment capacity identified in the Public Health Sustainability Framework [50]. We will measure these domains with the 40-item Program Sustainability Assessment Tool [67]; ratings use a seven-point scale (0=“to little or no extent,” 7=“to a very great extent”) and are averaged to produce an overall sustainment capacity score and domain subscale scores. We expect that differences in sustainment between state-focused and organization-focused grants will be mediated by increases in the “funding stability” domain over time and moderated by overall sustainment capacity.

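### Both Aim 1b moderators are surveyed after the penetration window has closed (3 to 4 years after for 77% of state-focused organizations), so the interaction can be estimated but not read as effect moderation

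*Protocol article*

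**What the plan says.** **Outcome.** Under Outcomes, Penetration, the outcome is the share of providers "certified in A-CRA during active implementation", and "the grant funding period will be treated as active implementation". It is therefore fixed when the grant ends.

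**Moderators.** Under Mechanisms, Penetration: "We will test two a priori moderators of A-CRA penetration outcomes: outer-context reimbursement for services" (external support, reported by supervisors) and leadership support (Implementation Leadership Scale, reported by clinicians). Under Mechanisms: "All variables will be captured through the web-based surveys". Table 2 lists both measures in the row "Web survey (Wave 1"), tied to Aims 1b and 3.

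**Timing.** Table 1 ("Waves of planned data collection for state-focused grant cohorts") gives the years since funding ended at Wave 1: 4 for cohort 1 ("7 states 37 organizations"), 3 for cohort 2 (33 organizations) and 0 for cohort 3 (21 organizations). Clinician surveys adds that some items for organizations no longer delivering A-CRA refer to the 6 months before they stopped.

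**Second role for external support.** Under Mechanisms, Sustainment, change in external support during the sustainment period is expected to be a mediator, "because state-focused grants might influence the availability of funding".

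**Hypothesis.** Quantitative data analysis predicts that the grant-type difference in penetration is moderated by external support and leadership quality. It tests this with interaction terms.

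**The concern.** A moderator should describe the organization before, or at least while, the outcome was being produced. Here both are recorded after exposure and after the outcome. An interaction with such a variable can arise in several ways:

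- The grant effect truly differs between organizations.
- Grant type changed the moderator. State-focused grants spent a third of their funds on state infrastructure, with funding among the examples (State-focused grants).
- Penetration changed the moderator.
- Staff changed. Respondents are current or recent employees, so the supervisor rated at Wave 1 need not be the one in post during the grant.

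At stake is the policy reading. A significant interaction would be taken to say where each grant type works better, and these data cannot separate that from the other explanations.

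**Working it through.** **1. Timing in the state-focused sample (Table 1).**

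- Organizations: 37 + 33 + 21 = 91, which matches the number selected under Treatment organizations.
- Surveyed 3 or 4 years post-funding: (37 + 33)/91 = 70/91 = 76.9%.
- Surveyed at 0 years: 21/91 = 23.1%. Before grant end: none.
- Mean lag to survey: (37×4 + 33×3 + 21×0)/91 = 247/91 = 2.7 years.

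Cohort 1 has 37 organizations in 7 states, although the sampling rule allows five per state (35). With 35, the share is 68/89 = 76.4%, so nothing changes.

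**2. Reference period.** The lags above run to the survey date. For organizations still delivering A-CRA, the article states no anchor to the grant period. For those that stopped, some items look back to the 6 months before stopping. If these include the moderator items, the reference period varies with later sustainment status. The items are in Additional file 3, which is not shown.

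**3. Two roles for one instrument.** Table 2 uses the external support items at Wave 1 for Aim 1b. Table 3 uses the same items at all waves for Aim 2. For the 70 organizations in cohorts 1 and 2, the Wave 1 reading already lies inside the sustainment period, where the protocol says the grant might affect funding. The same reading therefore serves as a moderator of earlier penetration and as part of a possibly grant-affected mediator.

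**4. The plan's power figure.** Statistical power states a detectable moderation effect of 0.89 SD. With a high/low moderator split evenly, the interaction has twice the standard error of the main effect:

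MDE = 2 × (1.960 + 0.842) × √(1/n₁ + 1/n₂)

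- 85 vs 82 organizations (abstract): 0.867 SD; power at 0.89 SD is 82.0%.
- 85 vs 78 (78 from Treatment organizations): 0.879 SD; power 81.0%.

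The stated figure reproduces. It makes no allowance for a moderator measured at the wrong time.

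**5. Illustration of dilution.** Assume the Wave 1 moderator correlates r with its grant-period value and the interaction shrinks by the factor r. The documents give no r. Taking 0.89 SD as the 80% power point, power = Φ(r × 2.802 − 1.960), and the true interaction needed for 80% power is 0.89/r.

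| r | Power at a true 0.89 SD | True interaction needed (SD) |
|---|---|---|
| 0.9 | 71% | 0.99 |
| 0.8 | 61% | 1.11 |
| 0.7 | 50% | 1.27 |
| 0.6 | 39% | 1.48 |
| 0.5 | 29% | 1.78 |

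This covers dilution only. Bias from a moderator that grant type or penetration has altered is additional and can go either way.

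**6. Restriction to cohort 3.** With 21 vs 82 organizations, the formula in step 4 gives 5.603 × √(1/21 + 1/82) = 1.37 SD.

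**The case against.** The strongest reply has five parts.

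- **Causal claims are disclaimed.** Current project says the study does not aim to isolate the causal impact of grant type, and Statistical power concedes that moderation power is weak. This stands in part. A reader might infer that Aim 1b cannot be answered at all; that goes too far, since the interaction is estimable. But Mechanisms presents these tests as bearing on how the grants influence outcomes, and Quantitative data analysis states moderation as a hypothesis. The disclaimer does not cover that reading.
- **The two roles of external support are not a contradiction.** The mediator is later change, for another outcome, and the wording is only that grants might influence funding. This stands. A reader might infer that the protocol firmly expects grant type to alter the Aim 1 moderator; it does not say so. What remains is overlap in time for 70 organizations.
- **Lag to the survey is not lag to the period asked about.** This also stands. An organization that stopped at grant end and received anchored items could be describing the late grant period.
- **Reverse influence on leadership is speculative.** The comparable scale measures perceived leadership toward evidence-based practices in general, and nothing says penetration is expected to change it. The direction is indeed unproven, but supervisors count in the penetration outcome and the timing cannot rule it out.
- **The figures cover one arm.** The earlier project had three interview waves up to 5 years post-funding, with no dates for the moderator surveys. The lag difference between grant types cannot be computed.

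A reader might also infer that these interactions use up part of the Aim 1 error rate. The article applies the step-up method per aim after all models are fitted, but does not say whether interaction tests are included.

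**Conclusion.** The point holds as a limit on interpretation. Both Aim 1b moderators are collected after the outcome closed: 70 of 91 state-focused organizations (77%) are surveyed 3 to 4 years post-funding, 21 at 0 years, and none before grant end. The interaction with grant type can be estimated, but without grant-period values or a stated recall anchor it cannot be read as effect moderation.

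The conclusion rests on Tables 1 and 2 and on the article stating no grant-period anchor for the survey items. If Additional file 3 anchors these two scales to the grant period, the timing problem becomes one of recall over 3 to 4 years for most organizations. The power losses in the table depend on an assumed correlation.

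**What to change.** 1. In Mechanisms, Penetration and in Quantitative data analysis, restate Aim 1b as an exploratory association between context measured later and penetration achieved earlier. State the reference period of each moderator item, by sustainment status.
2. Keep these interaction tests out of the Aim 1 step-up family, if they are in it.
3. Add a descriptive check restricted to cohort 3, noting its low power (about 1.37 SD detectable, against the stated 0.89).
4. Use a pre-award organization characteristic as a moderator only if one can be verified and linked for both grant types. N-SSATS is a candidate source, but whether it holds a usable item is unverified. Organization-focused awards ran 2006–2010, so the year before award is 2005–2009, and the planned extract starts in 2009. Earlier years would be needed for most of these grantees, and this would not replace the leadership measure.

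The first three changes cost wording and one small analysis. The downside is a weaker stated claim for Aim 1b.
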